**DATA COLLECTION PROCEDURE:**

This randomized trial will be conducted according to consolidated standards of reporting trial CONSORT guidelines (2010) [^20^](#_ENREF_20). This will be parallel group randomized controlled trial with 1:1 allocation ratio into two groups. Study will be conducted at physical therapy department of Mayo Hospital Lahore.

In order to recruit the patients in the study. Patients between ages 35-50 years, willing to participate will be chosen according to inclusion criteria. Patients will be asked to sign a consent form and give their will regarding being enrolled in the study.

**Randomization:**

Randomization sequence will be created by using Excel 2016 with a 1:1 allocation using simple randomization by an independent researcher. Patients will be divided into two treatment groups, group A and group B randomly.

Patients will be allocated to two groups by concealment of allocation through sealed envelopes.

## Concealment of allocation:

Allocation concealment will be achieved with sequentially numbered, opaque, sealed, envelopes SNOSE. SNOSE will be used according to guidelines of Doig and Simpson [^21^](#_ENREF_21).

An independent researcher with no clinical involvement in the trial will make the concealed envelopes. 88 Envelopes will be made. Half envelops will contain folded papers with Treatment A written on them and the remaining half will contain folded papers with Treatment B written on them. A carbon paper will be inserted in each envelop with carbon side facing the paper so the allocation sequence, patient name, date of birth of participant and other information can be transferred onto allocation paper inside the envelope.

A piece of tin foil is also inserted into envelop so the treatment card cannot be read against light. Envelops will be sealed and signed by the maker. A unique randomized number will be allocated to these envelops and shuffled vigorously. Then the envelops will be arranged sequentially and handed over to another independent researcher.

Assessor will pretest the participant and if eligible envelope will be allocated to subject. Therapist will record the information on the envelope and open it afterwards to maintain the concealment. Assessor will record the post treatment findings and another independent analyst will analyze the data.

This allocation of concealment will ensure the unpredictability of treatment allocation by investigators and patients.

## Blinding:

In this study patients, assessors, data analysts will be blinded to allocation of treatment groups in this study. Except for the therapist all other staff will be kept blinded as they will not be informed about the details of allocation. Trial will be adhered to established procedures to maintain separation between staff who will collect outcome measurements and the therapist. Patient will be blinded to treatment allocation as treatment will be given in separate rooms for each group. Therapist who is not blinded will not take the outcome measurements. All the other assessors, investigators and analysts will not know the details of treatment.

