**OBJECTIVES**

The objective of the study was to compare the effectiveness of neural mobilization technique with conservative treatment on pain intensity, cervical range of motion, disability, cervical muscle endurance and quality of life

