# **ETHICAL CONSIDERATIONS**

1. It will be gained prior from the Ethical Committee of the University before study
2. Written informed consent will be taken from all the patients
3. All information and collected data will be kept confidential.
4. Participants will remain anonymous throughout the study.
5. The subjects will be informed that there are no disadvantages or risks on the procedure of the study.
6. They will also be informed that they will be free to withdraw at any time during the process of the study.

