**Group A (Experimental group):**

In group A neural mobilization technique with sliding of median nerve will be applied with 3 seconds hold in each repetition, Neural mobilization will be done according to technique described by David Butler [^22^](#_ENREF_22). Subject will be placed in supine position and slider neural mobilization of the median nerve will be given. In this group conservative treatment which will include cervical isometrics exercises with 10 repetitions in each direction with 5 seconds hold will also be given. Isometric exercises will be performed with the patient in sitting position.

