**Group B (control group):**

In group B conservative treatment will be given which will include cervical isometrics exercises with 10 repetitions in each direction with 5 seconds hold will also be given. Isometric exercises will be performed with the patient in sitting position 3 sets of these exercises will be performed with the rest period of 30seconds.

All the subjects will be given hot packs for 10 minutes prior to the treatment.

Subjects having the same baseline will be given treatment for 12 sessions (3 times per week for 4 weeks). Pre assessment will be done at baseline, second assessment will be done after 2 weeks and final post assessment will be done at the end of 12^th^ session in 4^th^ week.

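### Separate rooms do not blind patients to a mobilization that only Group A receives, so the pain VAS, NDI and SF-36 are unblinded outcomes, and the objective misnames the comparison

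*Protocol*

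**What the plan says.** The Blinding section of the protocol lists three blinded parties: "In this study patients, assessors, data analysts will be blinded to allocation of treatment groups in this study". For patients it gives one mechanism: "Patient will be blinded to treatment allocation as treatment will be given in separate rooms for each group". The therapist is acknowledged to be unblinded and takes no outcome measurements.

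The arms are described in the two group sections. For Group A: "Subject will be placed in supine position and slider neural mobilization of the median nerve will be given", and then "In this group conservative treatment which will include cervical isometrics exercises with 10 repetitions in each direction with 5 seconds hold will also be given". For Group B: "In group B conservative treatment will be given which will include cervical isometrics exercises with 10 repetitions in each direction with 5 seconds hold". The exercises are done sitting in both arms, and everyone gets a hot pack beforehand. The number of sets (3) and the rest period (30 seconds) appear only under Group B.

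The stated objective is to "compare the effectiveness of neural mobilization technique with conservative treatment on pain intensity" and on further outcomes. The Outcome measures section makes pain on the VAS, endurance on the cranio-cervical flexion test and range of motion on the inclinometer the main outcomes. Quality of life is secondary. The NDI has its own section but is not classed as main or secondary.

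**The concern.** A separate room stops a patient from watching the other arm being treated. It does not hide from the patient what is done to his or her own arm and neck. With a manual technique in one arm and no sham in the other, the room arrangement cannot deliver the patient blinding that the protocol claims.

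This matters because the person who knows the treatment is also the person who scores the VAS, the NDI and the SF-36. Expectation or a wish to please can move those scores, whoever hands over the form. The protocol commits to CONSORT reporting, so the blinding statement is likely to be carried into the trial report, where readers would credit the pain result with a protection it does not have.

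A second problem concerns what is compared. The objective reads as mobilization against conservative treatment, but both arms receive conservative treatment. A conclusion that mobilization is better than conservative treatment could not follow from these arms.

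**Working it through.** **1. The arms side by side (protocol, Group A and Group B sections)**

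| Component | Group A | Group B |
|---|---|---|
| Hot pack, 10 minutes | yes | yes |
| Isometric exercises, sitting, 10 repetitions, 5-second hold | yes | yes |
| Sets and rest | not stated | 3 sets, 30 seconds |
| Median-nerve slider, supine, 3-second hold | yes | no |
| Sham or matched manual procedure | not applicable | none described |

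The mobilization row is a difference the patient feels and sees. Room separation leaves it unchanged. Nothing in the Blinding section says that patients are kept unaware of the hypothesis or of what the other arm receives.

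**2. Which outcomes are exposed**

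- Rated by the patient: VAS (main), SF-36 (secondary), NDI (not classed).
- Measured by the assessor: cranio-cervical flexion test and inclinometer range of motion (both main). These are less exposed, because assessor blinding is a separate provision that this argument does not touch.

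One of the three main outcomes is therefore a self-report scale.

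**3. The plan's own sample size**

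Inputs from the Sample size section: 3.35 (SD 1.49) and 4.45 (SD 1.63), alpha 0.05, power 90%, 44 per group.

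- Pooled SD = √((1.49² + 1.63²)/2) = √((2.2201 + 2.6569)/2) = √2.4385 = 1.562.
- d = (4.45 − 3.35)/1.562 = 1.10/1.562 = 0.704; the protocol states 0.70.
- A two-sided two-sample t-test with d = 0.70 needs 44 per arm (power 90.1%). The stated 88 reproduces and is not in dispute.

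**4. Illustration of what an expectation effect could do**

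Two assumptions are needed, and the documents supply neither: the size of the spurious shift b, and that the SD of 1.562 applies to the VAS. The Sample size section does not name the outcome or scale behind its means. With no true effect, the standardized shift is b/1.562. The noncentrality parameter is (b/1.562) × √(44/2), and the two-sided critical value on 86 degrees of freedom is 1.988.

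| Shift b | b/1.562 | Noncentrality | Chance of p < 0.05 | b as share of 1.10 |
|---|---|---|---|---|
| 0 | 0 | 0 | 5% | 0% |
| 0.2 | 0.128 | 0.60 | 9.1% | 18% |
| 0.3 | 0.192 | 0.90 | 14.5% | 27% |
| 0.5 | 0.320 | 1.50 | 31.8% | 45% |

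(The third rate is 14.47% before rounding, hence about 14%.)

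**5. The objective against the arms**

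If the word linking mobilization and conservative treatment in the objective means against, the objective does not match Group A, which also gets conservative treatment. If it means together with, no comparator is named. Either reading needs rewording.

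**The case against.** The best defence is that patients may still be partly blinded. Both arms get active, supervised care, the envelopes carry only the labels Treatment A and Treatment B, and a patient in a separate room may not know what the other arm receives or which arm is experimental. That is possible and the fix should allow for it. But the protocol does not say so; it claims blinding to allocation and rests it on the rooms.

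Three stronger readings are tempting and are not supported:

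- A reader might infer that the consent process unblinds patients. The protocol says only "Written informed consent will be taken from all the patients"; the consent text is not available, so what patients are told about the arms is unknown. The point does not need it.
- A reader might infer that Group A gets more therapist contact overall. No session length is given for either arm, and sets and rest are stated for Group B only, so contact time cannot be derived.
- A reader might infer that assessor blinding also fails. Nothing in the text shows that. For the same reason, asking the assessor to guess the arm would test a provision that is not in dispute here.

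It is also fair that the rejection rates are generic: any assumed bias raises them, in any trial of this size. They show scale and do not measure a defect of this protocol. Finally, the add-on structure can be worked out from the group sections, so the objective is loosely worded rather than concealed. It is still the sentence from which a conclusion will be drawn.

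**Conclusion.** The Blinding section is wrong as written. Patients know whether a nerve mobilization is performed on them, and the only mechanism offered cannot prevent that. The consequence falls on the VAS, which is a main outcome, and on the NDI and SF-36. The cranio-cervical flexion test and range of motion are less exposed. The illustrative false-positive rates of about 9%, 14% and 32% rest on assumed shifts of 0.2, 0.3 and 0.5 points and on using the SD of 1.56 for the VAS; the conclusion stands without them. The objective also needs rewording, because the arms compare mobilization plus conservative treatment with conservative treatment. Calling this a pure add-on contrast is premature until the exercise sets and rest are stated consistently for both arms.

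**What to change.** 1. Rewrite the Blinding section: assessors and analysts are blinded; the therapist and patients are not. If patients really are kept unaware of the hypothesis, say that they are blinded to the hypothesis only and describe how.
2. Instruct patients not to describe their treatment to the assessor.
3. State that the VAS, NDI and SF-36 will be interpreted as unblinded, patient-reported outcomes.
4. Reword the objective as neural mobilization plus conservative treatment versus conservative treatment alone.
5. Reconcile the Group A and Group B sections on exercise sets and rest before the contrast is described as a pure add-on. Which specification applies is for the investigators to settle.

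The cost is a few text changes and one instruction to patients. On this point the sample size does not change. The rewording does not remove the expectation bias; it makes it visible. The downside is that the trial can no longer be called patient-blinded.

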**Group A (Experimental group):**

In group A neural mobilization technique with sliding of median nerve will be applied with 3 seconds hold in each repetition, Neural mobilization will be done according to technique described by David Butler [^22^](#_ENREF_22). Subject will be placed in supine position and slider neural mobilization of the median nerve will be given. In this group conservative treatment which will include cervical isometrics exercises with 10 repetitions in each direction with 5 seconds hold will also be given. Isometric exercises will be performed with the patient in sitting position.

**Group B (control group):**

In group B conservative treatment will be given which will include cervical isometrics exercises with 10 repetitions in each direction with 5 seconds hold will also be given. Isometric exercises will be performed with the patient in sitting position 3 sets of these exercises will be performed with the rest period of 30seconds.

All the subjects will be given hot packs for 10 minutes prior to the treatment.

Subjects having the same baseline will be given treatment for 12 sessions (3 times per week for 4 weeks). Pre assessment will be done at baseline, second assessment will be done after 2 weeks and final post assessment will be done at the end of 12^th^ session in 4^th^ week.

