**Sample size:**

88 patients (44 in Group A and 44 in group B) will be included in the study using effect size 0.70, calculated from the parent article using (mean±SD) in group 1 (3.35±1.49) and group 2 (4.45±1.63) ^26^, at level of significance 0.05 and power 90% calculated by using G* Power [^19^](#_ENREF_19).

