**Data analysis procedure:**

Data will be analyzed on SPSS version 21 and MS Excel 2010. Descriptive analysis (mean, median, mode, variance, standard deviation) will be performed for quantitative data i.e. continuous and discrete variables. Frequencies and percentages will be calculated for categorical and nominal data. For graphical representation, continuous and discrete variables will be presented with histograms with normal curve and categorical and ordinal data will be presented in form of bar and pie charts.

Independent samples t-test and Man Whitney test will be used accordingly for between group comparisons. Repeated measure ANOVA will be used for within group analysis.

Inferential statistics will include independent samples t test and Man Whitney test at various levels of assessment for between group comparison while Freidman and repeated measure ANOVA will be performed for within group analysis separately. Excel 2010 will be used for scatter plotting and routine calculations.

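### The 12-session course is tied to an undefined 'same baseline' condition that matches no eligibility criterion, conflicts with the flow chart, and could be applied as selection after allocation

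*Protocol*

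**What the plan says.** After describing both arms, the protocol sets out the schedule at the end of the section Group B (control group): "Subjects having the same baseline will be given treatment for 12 sessions", three times a week for four weeks. This sentence is the only one that says who receives the course, and it is conditional.

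Four other places bear on it:

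- **Sampling criteria.** Neither the inclusion nor the exclusion list contains a requirement on baseline values of the outcomes.
- **Concealment of allocation.** The order of events is given as "Assessor will pretest the participant and if eligible envelope will be allocated to subject". Pretest and eligibility therefore come before the envelope.
- **Research Work Plan (flow chart).** It plans 88 patients randomised, 44 allocated to each arm and 44 in each arm receiving what they were allocated.
- **Data analysis procedure.** "Independent samples t-test and Man Whitney test will be used accordingly for between group comparisons". No baseline-adjusted comparison is named, although Baseline measurements has pain, range of motion, endurance and quality of life recorded before treatment.

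The sample size section states "88 patients (44 in Group A and 44 in group B) will be included in the study", at 90% power.

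**The concern.** A condition for receiving treatment that is neither defined nor part of eligibility can be applied in more than one way. One of those ways is harmful. Patients enter one at a time, and the clause appears after the arms have been described, so it can be taken to govern delivery of treatment that has already been allocated. Being the same as someone also needs a comparator. If the comparator is the other arm, sameness cannot be judged until patients have been allocated.

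If patients were picked this way and the others were left out of the analysis, the arms compared would no longer be the arms that were randomised. Any imbalance produced by the picking would be mixed with the treatment effect. The analysed number would also fall below the 44 per arm that supports the stated power.

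A smaller, related point is that the protocol names an unadjusted test while collecting the baseline values that would allow chance differences between the arms to be handled in the model, with nobody set aside.

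**Working it through.** **1. The passages side by side.**

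| Place in the protocol | Who is treated, or when |
|---|---|
| Sampling criteria | No condition on baseline outcome values |
| Concealment of allocation | Pretest, then eligibility, then envelope |
| Group B, schedule sentence | Only subjects with the same baseline; variable, tolerance, comparator, timing and judge not given |
| Flow chart | 88 randomised; 44 of 44 treated as allocated in each arm |

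If the schedule sentence works as a condition on allocated patients, the flow chart's 44 of 44 holds only when nobody fails it. If it works before allocation, it belongs in the eligibility criteria and is absent from them. On either reading something has to be reconciled.

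**2. Reproducing the planned sample size.** Inputs from Sample size: "using effect size 0.70"; "group 1 (3.35±1.49) and group 2 (4.45±1.63"; "at level of significance 0.05 and power 90" per cent. From Data collection procedure: "parallel group randomized controlled trial with 1:1 allocation ratio into two groups".

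- Pooled SD = √((1.49² + 1.63²)/2) = 1.562. Difference = 4.45 − 3.35 = 1.10. Effect size d = 1.10/1.562 = 0.704, stated as 0.70.
- Two-sample t-test, two-sided 0.05, noncentral t with df = 2n − 2 and noncentrality d√(n/2). Sidedness is not stated. One-sided testing needs only 36 per arm, so two-sided is the version that gives 88.
- At n = 44: noncentrality = 0.70 × √22 = 3.283, df = 86, critical t = 1.988, power = 0.901. At n = 43, power is 0.894.

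The stated 88 is reproduced exactly. It is the smallest total that reaches 90%, and no allowance for losses is stated.

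**3. What removal would cost, if it happened.** The protocol gives no fraction, so the fractions are assumptions, with equal removal from both arms and d held at 0.70:

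| Removed | Per arm | Power |
|---|---|---|
| none | 44 | 0.901 |
| one per arm | 43 | 0.894 |
| about 5% | 42 | 0.887 |
| about 10% | 40 | 0.871 |
| about 20% | 35 | 0.823 |
| about 30% | 31 | 0.774 |

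**4. What baseline adjustment would give with all 88 kept.** With correlation r between an outcome and its own baseline, ANCOVA reduces the residual SD by the factor √(1 − r²), so the effective d is 0.70/√(1 − r²). The protocol gives no r; 0.3 to 0.6 is assumed.

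| r | Effective d | Power at 44 per arm |
|---|---|---|
| 0 (unadjusted) | 0.700 | 0.901 |
| 0.3 | 0.734 | 0.926 |
| 0.5 | 0.808 | 0.963 |
| 0.6 | 0.875 | 0.982 |

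These use 86 degrees of freedom. Spending one on the covariate lowers each ANCOVA power by less than 0.001.

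**The case against.** A reader might infer that the protocol drops patients after randomisation, that the unblinded therapist decides who is dropped, and that the analysis set shrinks as a result. The document states none of these.

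- **Timing.** The only stated sequence puts pretest and eligibility before the envelope. A rule on pre-allocation values, applied blind to arm, would narrow the population without biasing the comparison.
- **Who decides.** No section gives the therapist this role. The assessor, who is to be blinded, carries out the pretest.
- **Analysis.** The sentence concerns delivery of treatment. Not being treated is different from not being analysed, and no section excludes anyone from the analysis on baseline grounds.
- **Intent.** The flow chart plans treatment for everyone allocated, so the sentence may be only a loose way of saying that comparable groups will receive the course.

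These points stand, and they make the harm conditional. Nor does the protocol specify a numerical tolerance or a significance test of baseline equality, so no failure rate can be attached to such a check. The power losses above hold d fixed. If patients with extreme baselines were removed and baseline correlates with outcome, the remaining spread would narrow and the loss would be smaller.

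On the analysis, an unadjusted t-test or rank test is valid in a randomised trial, and covariate adjustment is often left to the SAP, which is not shown. Adjustment is therefore recommended as a gain over the test this protocol names, not as the correction of an error.

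The objections do not remove the defect itself. The clause is undefined, has no counterpart in the eligibility criteria and does not fit the flow chart.

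**Conclusion.** The point holds as an undefined condition and an internal conflict that should be repaired. It does not hold as proof of a planned post-randomisation exclusion.

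The damage to the randomised comparison depends on two assumptions: that the clause is applied after allocation, and that unmatched patients also leave the analysis. Under both, and with d = 0.70, losing even one patient per arm takes power just under 90%, and losing about 10% takes it to about 0.87. The actual size cannot be worked out from the protocol, because it gives no fraction.

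The gain from baseline adjustment does not depend on how the clause is read. It depends only on the assumed correlation of 0.3 to 0.6.

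**What to change.** 1. In the schedule sentence, replace the same-baseline clause with all randomised subjects. If a baseline restriction is truly intended, write it as a defined eligibility criterion under Sampling criteria, applied at the pretest before the envelope is assigned.
2. Reconcile the sentence with Concealment of allocation and with the flow chart, so that all three describe the same sequence and the same numbers treated.
3. State that every randomised patient is analysed in the allocated group.
4. In Data analysis procedure, replace the unadjusted t-test for continuous outcomes with ANCOVA on group and that outcome's own baseline value. Keep a rank-based alternative for clearly non-normal outcomes.

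The cost is a few sentences and a little more analysis work. No extra patients or measurements are needed, because the baseline values are already to be collected, and the sample size stays at 88.
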